### Participants

The participants for the qualitative components of this process and implementation evaluation, including focus group discussions (FGDs) and in-depth interviews (IDIs), will include a range of individuals involved in the SHP intervention. Both FGDs and IDIs are used to capture the perspectives of different stakeholders. FGDs will be conducted with ASHAs who participate in the training and are using the SHP app and diagnostic devices during their visits to explore both their shared and individual experiences in balancing their existing routine responsibilities and SHP activities, as well as their interactions with primary care doctors, auxiliary nurse midwives (ANMs), and women. IDIs will be conducted with women, primary care doctors, ANMs, health officials, women, and field supervisors in order to provide a space for participants to share sensitive details, personal reflections, and a secure environment to discuss their experiences (women). In addition, practical considerations around feasibility determined the mixed use of FGDs and interviews.

Sampling will be guided by thematic saturation, defined as the point at which no new themes or relevant insights emerge from successive interviews or FGDs. Based on the planned study design and practical feasibility, qualitative data collection will be conducted in 2 rounds (midline and endline), with an anticipated total of 32 IDIs and 12 FGDs across both field sites, as detailed in Table 3 (see below, under qualitative data collection plan). This will include 8 IDIs with pregnant and postpartum women, 8 IDIs with primary care doctors, 4 IDIs with ANMs, 8 IDIs with field supervisors, 4 IDIs with policy or health officials, and 12 FGDs with ASHAs. Final sample sizes may vary depending on achievement of thematic saturation.

Participants will be selected from those already involved in the SHP2 trial. Policy makers will be identified with the assistance of the district and state administrative heads. For healthcare workers, all healthcare workers who participated in the SHP study were eligible. For women, all participants of the study are eligible to participate, regardless of whether they have completed all assessments or not. In addition, women who have rejected participation are eligible. Participants who decline participation in the process evaluation are ineligible.

The study team will also identify independent experts from these areas to facilitate qualitative interviews. These interviews and FGDs will be conducted at convenient locations for participants. All sessions will be audio-recorded, with informed consent of the participants.

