	ASHAs	Study staff will support ASHAs by attending visits (with participant permission) and providing support for using the technology until the ASHA feels confident of performing assessments independently.	Continuous	Initially for the visits, then as needed/identified in the fidelity checklist	Effectiveness, fidelity, adoption, acceptability, implementation
	Women, ASHAs, primary care doctors, district officials, community, field staff	Continuous feedback loops to enable corrections and changes that are necessary to achieve successful programme implementation and outcomes	Continuous	Regularly	Effectiveness, fidelity, adoption, acceptability, implementation, maintenance
II. Strategies to improve adherence to the intervention	ASHAs	Quality control visits will be made to observe the intervention delivered by ASHAs and assessed by the study team.	Periodic	1 visit	Fidelity, effectiveness
		Compliance of the ASHAs with the intervention activities will be assessed with a fidelity checklist, administered by the study team	Before and after refresher training	Twice	Fidelity
	ASHA, primary care doctors	Compliance with the intervention visits will be monitored centrally by tracking the visits recorded in the SHP app. If trends of non-engagement across multiple participants from the same ASHA worker or PHC are noted, the study team will arrange a site visit.	Continuous	Regularly	Fidelity
III. Strategies to build capacity	ASHAs	Every 6 months, the study team will conduct a 1-day refresher training session for the ASHAs.	One day every 6 months	1 day	Reach, effectiveness, implementation
IV. Strategies for dissemination	Community	Community stakeholder engagement events will be held to increase awareness of the programme and the importance of high-risk pregnancy conditions, and co-develop pathways to implementation and sustainability after completion of the trial.	Before start, and after completion of the trial	Regularly	Implementation, maintenance, acceptability
	Women	Stakeholder engagement events will be held to increase awareness of the programme and the importance of high-risk pregnancy conditions, and co-develop pathways to implementation and sustainability after completion of the trial.	Before start, during, and after completion of the trial	Regularly	Implementation, maintenance, acceptability

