### Qualitative data collection

The process evaluation framework will guide the qualitative data collection. Data collection will be done using pre-/ mid-/ post-implementation questionnaires in two rounds: round 1 (planned April to May 2023 and September to December 2023) and round 2 (planned November 2024 to January 2025), audio analysis of interviews and focus groups, observation of daily routines and interactions, fidelity checklists, journey mapping, and diary/project log analysis.

IDIs and FGDs will be conducted with representatives from beneficiaries (women participating in SHP trial), healthcare providers (ASHAs, ANMs, medical officers, healthcare providers), and field supervisors/staff in each field sites involved in implementing and influencing policy decisions concerning maternal and child health and NCDs in the state. A representative sample of participants from the study sites and clusters will be purposely selected to capture differences in PHC qualities. The questionnaires will be developed using the RE-AIM framework and Proctor et al.’s implementation outcomes.^
34
^ Interviews and focus groups will be conducted in Telugu/Hindi, audio-recorded, transcribed verbatim in the original language, and translated into English for analysis. To ensure accuracy and preserve meaning, a subset of transcripts will be independently reviewed against the original recordings, and discrepancies will be resolved through discussion within the research team. Key terms and culturally specific expressions will be discussed among the team and meanings verified with bilingual speakers and the data collectors to ensure conceptual equivalence.

Additional qualitative methods applied will be observation and patient journey mapping of high-risk women to understand how they enter, navigate, experience, and exit the SHP programme. Furthermore, we will explore their experiences within existing private and public healthcare. These methods will capture patient behaviours, feelings, motivations, and attitudes across care episodes.

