### Mixed methods data collection for process and implementation evaluation

#### To assess whether the SHP study has been implemented as planned (implementation fidelity, dose)

To assess whether, and to what extent, the study has been implemented as intended, we will assess fidelity and dose (number of visits) of the trial procedures themselves. This will be collected using process data records, including frequency of training, completion of electronic case record files, and activity logs, drawing on SHP app-based data sources described above. Explain whether, how, and why the intervention has been effective (Reach, Effectiveness, Adoption, Acceptability, Implementation, Maintenance).

We will collect effectiveness and implementation outcomes.

Effectiveness outcomes: This will be based on the primary and secondary outcomes of the SHP trial.^
26
^Implementation outcomes: This will be assessed using the RE-AIM framework and Proctor et al.’s typology. Reach will assess the potential reach of the SHP intervention, that is, whether it is used in all eligible participants (proportion of the target population and its representativeness). Effectiveness will assess the impact on health outcomes, including positive, negative, and unintended consequences. Adoption will assess how well and to what extent the intervention has been taken up by the participants of the SHP trial (including how representative this is for the target population in the setting). Implementation will explore the extent to which each of the SHP components were implemented and/or adapted, including an assessment of the costs of delivery. Maintenance will assess the degree to which SHP was sustained at both setting level (in sites) and individual level (among participants). Acceptability will assess to what degree the intervention was acceptable for the participants of the trial (women, ASHAs, primary care doctors). Feasibility will assess to what extent the SHP intervention can be adopted, implemented, and sustained as intended. To assess this, a range of data will be used, including trial data, checklists, surveys, and costing and administrative data, with app-based process data drawn from the SHP platform as described above. Topic guides for qualitative interviews and focus groups will be informed by the process evaluation framework, Proctors’ framework^
34
^ and Weiner’s Implementation Measures,^
43
^ translated into local languages, and piloted before administration.

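### The Participants section gives two ASHA sampling frames that do not agree (current app users, or all participating workers), and under the narrower one no session is scheduled for ASHAs who stopped or never started

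*Protocol article*

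**What the plan says.** The Participants section of the protocol article introduces the focus groups with this description: "FGDs will be conducted with ASHAs who participate in the training and are using the SHP app and diagnostic devices during their visits". Individual interviews are assigned to other groups: "IDIs will be conducted with women, primary care doctors, ANMs, health officials, women, and field supervisors". ASHAs are not in that list. The planned sessions end with "and 12 FGDs with ASHAs", and Table 4 splits these into 6 at round 1 and 6 at endline.

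Further down the same section, the eligibility statement for staff is wider: "For healthcare workers, all healthcare workers who participated in the SHP study were eligible". For women, the section expressly admits those with incomplete assessments and those who refused to take part. There is no matching statement for ASHAs.

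On selection, the Qualitative data collection section says: "A representative sample of participants from the study sites and clusters will be purposely selected to capture differences in PHC qualities". On engagement, Table 3 (Implementation strategies) plans central tracking of visits recorded in the app and adds: "If trends of non-engagement across multiple participants from the same ASHA worker or PHC are noted, the study team will arrange a site visit". No section links that tracking to the choice of focus-group members.

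**The concern.** ASHAs deliver the intervention, so an ASHA who is trained and then stops, or never starts, is direct evidence on adoption. The stated objectives include the barriers and facilitators to implementation and the conditions for sustaining and scaling up the intervention. Both call for the reasons given by workers for whom it did not take hold, such as workload, device problems or lack of response from the doctor.

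If a site recruits by the focus-group sentence, those workers are not invited, and no other interview or group session is scheduled for them. The qualitative account would then tilt towards the experience of continuing users. In the context-mechanism-outcome analysis, failure to adopt would be explained largely by people other than the ASHAs concerned. A site recruiting by the eligibility sentence would draw from a different pool, so the two field sites could sample differently while both follow the text.

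**Working it through.** No error rate or sample-size formula applies. The check is a count of sessions and a side-by-side reading.

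**1. Reproduce the planned sessions** (Participants section and Table 4).
- Individual interviews: 8 women + 8 primary care doctors + 4 ANMs + 8 field supervisors + 4 officials = 32, as stated.
- Focus groups: 6 + 6 = 12, as stated, all with ASHAs.
- Total: 32 + 12 = 44 sessions.
- ASHA share: 12 of 12 focus groups, 0 of 32 interviews, 12 of 44 sessions overall.

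The plan's figures add up. Focus groups are the only interview or group sessions scheduled for ASHAs.

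**2. Compare the two frames for each kind of ASHA.**

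| ASHA | Focus-group sentence | Eligibility sentence |
|---|---|---|
| Trained, using the app regularly | in | in |
| Trained, using it rarely | in (no threshold is stated) | in |
| Trained, used it, then stopped | out | in |
| Trained, never started using it | out | in, if training counts as participating |
| Never took part at all | out | out |

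The sentences disagree on the third row and, on a natural reading, on the fourth. They agree on rare users, who are still using the app.

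**3. Check whether another selection rule settles it.** The purposive criterion in Qualitative data collection is the quality of the Primary Health Centre. It does not vary engagement within a centre. The tracking in Table 3 would identify low engagement, but its stated consequence is a site visit.

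**4. Check what the other sources would supply.**
- *App data* (Quantitative data collection) record ASHAs' screening and follow-up activity. They show that use stopped, but not why.
- *Fidelity checklists* (Table 3) are completed by the study team and measure compliance.
- *Surveys* are named for barriers and facilitators and may reach ASHAs, but none is assigned to those who stopped.
- *The Program Sustainability Assessment Tool* goes to ASHAs after the trial and concerns whether the programme can be maintained.
- *Women, ANMs, doctors, officials and supervisors* can report what they saw of an ASHA's difficulties, but second-hand.

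These sources cover the fact of non-use well and the ASHAs' own reasons only in part.

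**5. Check the analysis rule.** The Data analysis section picks key themes partly by frequency, with more than 60% of participants as an example. If a few stopped ASHAs do attend, their themes may not reach that mark. Knowing who attended would therefore help in reading the results.

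**The case against.** The strongest reply is that the eligibility sentence is the only one framed as a rule, and it admits a trained ASHA who stopped. The focus-group sentence explains why groups are used and may simply describe intervention-arm ASHAs. This stands against any claim of outright exclusion. A reader might infer that stopped and low-use ASHAs are barred and that their representation is zero. The document does not support that: the eligibility sentence points the other way, and a rare user satisfies even the narrower wording.

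A second stronger reading is that adoption, barriers and acceptability will be judged from continuing users alone. That also fails. The Mixed methods section says "Adoption will assess how well and to what extent the intervention has been taken up by the participants of the SHP trial", and it draws for this on trial data, checklists, surveys, administrative data and app data. Barriers also draw on other stakeholders, supervisor reports and logistics monitoring. What remains is narrower: the first-hand qualitative explanation from ASHAs.

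Third, the plan is flexible. Additional interviews are allowed if needed, sample sizes may vary, and app monitoring is triangulated with supervisor reports. Nothing forbids using the tracking to choose participants. This is fair, but permission is not a plan, and the text that is stated points recruitment to current users.

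Fourth, this is a condensed article, and detailed focus-group selection may sit in the full protocol. That would answer a complaint about missing detail. It does not answer two stated frames that conflict.

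Finally, setting aside whole groups for non-engaged ASHAs could identify individuals; the Ethical approval section itself recognises that anonymity is difficult in small rural communities. This stands, and the fix does not require such groups.

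**Conclusion.** The point holds as an unreconciled sampling frame with a real risk of a one-sided qualitative account. All 12 ASHA focus groups are introduced by a sentence limited to current users, no ASHA interview is scheduled to offset it, and no stated criterion brings engagement into the selection. If that sentence is followed, ASHAs who were trained and then stopped or never started have no scheduled session.

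The conclusion rests on two assumptions: that a site would act on the focus-group sentence rather than the eligibility sentence, and that some trained ASHAs did stop or not start. The document gives no figure for the second. Table 3 treats non-engagement as a contingency to be monitored, not as an expected rate. The size of any distortion cannot be calculated. It is nil if every trained ASHA kept using the app and grows with the share who did not. The correction is worth making because it is nearly free, but it does not undermine the quantitative assessment of adoption.

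**What to change.** 1. **Align the two sentences.** Describe the focus groups as open to *all ASHAs trained in the SHP trial, whether or not they are still using the app*, so that they match the eligibility statement.
2. **Add engagement to the selection.** Name level of app engagement, taken from the central tracking already planned in Table 3, as a purposive criterion alongside the quality of the Primary Health Centre.
3. **Use the existing allowance for additional interviews** where a low-use or stopped ASHA is better heard individually. Reserved non-user groups are optional and should be weighed against confidentiality.
4. **Report attendees' engagement status in aggregate only**, given the difficulty of anonymity in small communities.
5. **For sessions already held** (the Trial status section dates the first interviews and focus groups to November 2022), report who attended by engagement status in aggregate and state the limitation.

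The cost is a change of wording and a list drawn from data already collected. The 12 planned focus groups need not change; any individual interviews would come under the existing allowance. The downside is somewhat harder recruitment and fewer places for active users.

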### Informed consent process

Participants will provide consent before qualitative interviews or focus groups by personally signing the Informed Consent Form (ICF) after reviewing the participant information sheet. Both documents, outlining the interview process, participant role, and any potential risks, will be available in written and verbal formats in the local language.

The consent process will be managed by a qualified and experienced member of the research team, who will be authorised by the Chief Investigator. A copy of the signed ICF will be given to the participant. The original signed form will be retained at the study site. Also, where desirable and acceptable to participant groups, a summary of the discussion proceedings will be written and countersigned by all participating in the discussion meeting. The data collected during these interviews and focus groups will be handled in accordance with the data protection policy for the SHP trial. All personal and sensitive information will be kept confidential and stored securely to protect participants’ privacy. The policy will also ensure that participants’ rights are respected, including their ability to withdraw from the study at any point without penalty.

During data collection, all study participants will be allocated a unique study identifier. No personal data (names, addresses, contact details) will be stored in the study database. A password protected database containing personal information needed for participant follow-up will be maintained for use by designated study field investigators only for the duration of the period of participation of an individual in the study. All information collected on participants will be kept confidential and used only for the purposes outlined in the ICF by study staff and clinicians involved in the study.

### Data collection

The data collection for this mixed methods study includes both quantitative and qualitative data, collected from a variety of sources such as SHP app analytics, trial data, interviews and FGDs.

Assessment measures and planned forms of measurement has been previously published in the protocol for the SHP main trial.^
26
^

The sample size for this process and implementation evaluation is determined by the objectives of the evaluation, the types of data to be collected (quantitative and qualitative), and practical considerations including resources and time. For the quantitative study, we aimed to include either the full sample, and/or from all staff and a representative sample of women. For the qualitative evaluation, we included a smaller, more purposive sample.

### Quantitative data collection

Quantitative data will be sourced from the SHP trial database.^
26
^ Data will be extracted from the SHP app, which tracks ASHAs’ screening and follow-up activities and the number of primary care doctor visits. At the intervention sites, the ASHA worker will conduct a health assessment of the women during home visits, gather data on pregnancy, childbirth, and treatment (if any) received during or after childbirth, and enter this data in the SHP application. Data will be collected in the SHP app on the consumption of iron and folic acid tablets for improving blood haemoglobin, health examinations performed, haemoglobin levels, and blood pressure readings, as well as any other specific diseases or treatments received during pregnancy and after delivery. This information will help understand how the health status of the women has changed during the project’s duration when compared to women receiving usual care in the control sites. In addition, quantitative data from trial records, district records, surveys, checklists, and costing proforma will be collected, as outlined in the SHP trial protocol paper.^
26
^

### Qualitative data collection

The process evaluation framework will guide the qualitative data collection. Data collection will be done using pre-/ mid-/ post-implementation questionnaires in two rounds: round 1 (planned April to May 2023 and September to December 2023) and round 2 (planned November 2024 to January 2025), audio analysis of interviews and focus groups, observation of daily routines and interactions, fidelity checklists, journey mapping, and diary/project log analysis.

IDIs and FGDs will be conducted with representatives from beneficiaries (women participating in SHP trial), healthcare providers (ASHAs, ANMs, medical officers, healthcare providers), and field supervisors/staff in each field sites involved in implementing and influencing policy decisions concerning maternal and child health and NCDs in the state. A representative sample of participants from the study sites and clusters will be purposely selected to capture differences in PHC qualities. The questionnaires will be developed using the RE-AIM framework and Proctor et al.’s implementation outcomes.^
34
^ Interviews and focus groups will be conducted in Telugu/Hindi, audio-recorded, transcribed verbatim in the original language, and translated into English for analysis. To ensure accuracy and preserve meaning, a subset of transcripts will be independently reviewed against the original recordings, and discrepancies will be resolved through discussion within the research team. Key terms and culturally specific expressions will be discussed among the team and meanings verified with bilingual speakers and the data collectors to ensure conceptual equivalence.

Additional qualitative methods applied will be observation and patient journey mapping of high-risk women to understand how they enter, navigate, experience, and exit the SHP programme. Furthermore, we will explore their experiences within existing private and public healthcare. These methods will capture patient behaviours, feelings, motivations, and attitudes across care episodes.

Data collection was designed according to the objectives of the process evaluation. To understand how and why the SHP intervention may be effective, a relatively larger representation from healthcare providers is planned, as these are directly involved in using and delivering the SHP trial components. To understand for whom the implementation is useful, IDIs with women as the end beneficiaries will be conducted, and to gain in-depth accounts of their experiences. The number of IDIs and FGDs is also guided by feasibility. It is expected that in particular the interviews will provide a rich qualitative understanding and will complement the larger quantitative data of end beneficiaries conducted in the trial.

An iterative approach to data collection and analysis will be used until data saturation (i.e. when no new themes are emerging). Throughout the trial, the research team will regularly organise meetings with stakeholders and debriefing sessions with field supervisors to review emerging findings. If needed, additional interviews will be conducted.

An overview of the overall data collection plan for the SHP process evaluation is shown in Table 4.

**Table 4. table4-17455057261425789:** Overview of process evaluation data collection plan.

Stakeholders (intervention group)	*n* IDIs/FGDs in both fieldsites	*n* IDIs/FGDs in both fieldsites	
	Round 1: 12 months	Round 2: endline	Total *n* IDIs/FGDs
Women			
Pregnant and postpartum	4 IDIs	4 IDIs	8 IDIs
Healthcare providers			
ASHAs	6 FGDs	6 FGDs	12 FGDs
Primary care doctors	4 IDIs	4 IDIs	8 IDIs
ANMs	4 IDIs	0	4 IDIs
Project field team/managing the supply chain			
Field supervisors	4 IDIs	4 IDIs	8 IDIs
Policy officials			
Healthcare officials	0	4 IDIs	4 IDIs
Total intervention	16 IDIs and 6 FGDs	16 IDIs and 6 FGDs	32 IDIs and 12FGDs

ASHA: Accredited Social Health Activist; FGD: focus group discussion; IDI: in-depth interview; ANM: auxiliary nurse midwife.

